### Assessment of adverse events

Adverse events arising during the trial will be managed in accordance with standard clinical practice, recorded by the trial manager. Electronic cigarette use by participants will be recorded and participants will be able to report their experience at the 4-week, 3-month and 12-month follow-up assessments.

### Data management and monitoring

Monitoring of trial data shall include: confirmation of informed consent; source data verification; data storage and data transfer procedures; local quality control checks and procedures, back-up and disaster recovery of any local databases and validation of data manipulation. Entries on case report forms (CRF) will be verified by inspection against the source data. A sample of CRFs (10% or as per the study risk assessment) will be checked on a regular basis for verification of all entries made. In addition, the subsequent capture of the data on the trial database will be checked. Interview transcripts will be checked against audio-recordings for accuracy. Where corrections are required these will carry a full audit trail and justification. Trial data will be stored and maintained on Nottingham or Cardiff University respective servers. When and if data are transferred it will be conducted in a controlled/verified manner in accordance with a data management plan and the University of Nottingham’s ‘Handling Personal Data’ policy.

### Statistical analyses

We will compare baseline characteristics between randomised treatment groups descriptively. We will estimate the effect of the intervention by comparing our primary and secondary outcomes between intervention and SBP groups using logistic regression, presenting results in terms of the proportion achieving abstinence in the two groups, the risk difference and the OR, with 95% CIs.

Primary analysis will be on an intention to treat basis, assuming that missing data implies smoking, but we will conduct sensitivity analysis to examine the impact on our findings of alternative assumptions, including the Hedeker approach which assumes alternative relationships between having missing data and smoking, and using multiple imputation to test the alternative assumption that the data are missing at random (ie, missing data can be modelled using measured variables).

We do not plan a priori to adjust for any baseline covariate, presuming that randomisation will achieve balance between groups. We will look for effect modification of effect of intervention according to presence of absence of abnormal scan findings of emphysema or CAC, using the likelihood ratio test for interaction. In sensitivity analysis, we will analyse excluding those who were consented to the intervention group prior to change in timing of consent (n=94).

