### Blinding

The sequence of treatment allocations will be concealed until interventions have all been assigned and recruitment and data collection are complete. Once primary and secondary data from both treatment groups have been analysed by the trial statistician, the groups will be un-blinded to the Trial Management Group (TMG). Consent is taken at the 4-week visit by the SCP. In order to ensure concealment at the time of recruitment/consent, the personalised risk information booklet (further detail provided later) or a blank booklet are enclosed in a sealed envelope which is opened by the SCP following consent/data collection. This arrangement commenced five rounds into recruitment following review of processes at a Trial Steering Committee. For five rounds at the start of the trial, SCPs were aware of trial allocation at the time of consent/data collection. The impact of this will be assessed in a sensitivity analysis.

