### Sample size

Recruitment will be limited to the number of eligible smokers attending for an LHC over the 2-year YLST recruitment period. Based on early recruitment figures, we anticipate 1040 smokers enrolling in YESS.

Those in the SBP group will be provided with a service similar to that provided by national NHS SSS. A 2010 systematic review of relapse rates among smokers quitting with national NHS SSS found that 53% had quit at 1 month, and 15% at 1 year.^30^ Fitting an exponential decay function to these figures we estimate a monthly relapse rate, after 1 month, of 11.5%. Applying these figures to our study design we would expect a quit rate of 41% at 3 months in those receiving SBP. If the cessation rate is 41% in the usual care group, a study of 1040 individuals will provide 90% power to detect an increase to 51% (ie, an increase of 10%), and 80% power to detect an increase to 49.6% (ie, an increase of 8.6%).

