### Outcome measures

#### Primary outcome

Seven day point prevalent CO validated SC 3 months after the LHC in all participants enrolled in the YESS study.

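### The randomised comparison is left unadjusted on a balance argument alone, which gives up a modest, nearly free gain in precision

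*Protocol article*

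**What the plan says.** All references are to the protocol article.

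- **Statistical analyses.** Primary and secondary outcomes are compared between the two arms "using logistic regression, presenting results in terms of the proportion achieving abstinence in the two groups, the risk difference and the OR, with 95% CIs". On covariates: "We do not plan a priori to adjust for any baseline covariate, presuming that randomisation will achieve balance between groups". No other reason is given.
- **Primary outcome.** "Seven day point prevalent CO validated SC 3 months after the LHC in all participants enrolled in the YESS study".
- **Sample size.** Recruitment is limited to eligible smokers attending over the two-year screening period, expected to be 1040. With 41% abstinent under standard best practice, the stated power is 90% for 51% and 80% for 49.6%. The 41% is derived from a review in which "53% had quit at 1 month, and 15% at 1 year", using a monthly relapse rate of 11.5% after month 1.
- **Data collection, Table 1.** Smoking behaviour, motivation, quit confidence and self-efficacy are recorded at baseline and at each follow-up.
- **Randomisation; Secondary outcomes.** Allocation takes place after the screening visit and before the 4-week follow-up. Cessation at 4 weeks is a secondary outcome.
- **Blinding.** At the 4-week visit the booklet is "enclosed in a sealed envelope which is opened by the SCP following consent/data collection". For the first five rounds this was not in place, and the practitioners knew the allocation at consent and data collection.
- **Comparative measurement (community services).** The observational comparison is adjusted for age, gender, heaviness of smoking and education. The same section promises a detailed SAP before recruitment is complete.

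**The concern.** Balance is the wrong test for whether to adjust. Randomisation balances prognostic factors in expectation, and that is enough for an unadjusted comparison to be valid. Variation in the outcome that measured predictors could explain still stays in the standard error. Adjusting for those predictors and then averaging over the sample to get a marginal risk difference removes that part at no cost in participants.

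This matters more than usual here because recruitment is fixed by screening throughput, so the sample cannot simply be enlarged. The plan also recognises that cessation has known predictors, since it adjusts for them in the observational comparison. What is at stake is the width of the primary confidence interval and some points of power. The validity of the result is not at stake.

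**Working it through.** **Inputs.** 520 per arm (1040, 1:1), control rate 0.41, alternatives 0.51 and 0.496, and 53% quit at 1 month (Sample size). Two-sided 5% is assumed: Sample size states no alpha, but Statistical analyses promises "the risk difference and the OR, with 95% CIs". The explained variance (R²) of the baseline covariates and the late-quit rate *b* are not in the document and are assumed over a range.

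**1. Reproduce the stated power.** With pooled variance under the null,

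z = [d√n − 1.96·√(2p̄(1−p̄))] / √(p₁(1−p₁) + p₂(1−p₂)).

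- 41% v 51%: (0.100 × 22.80 − 1.96 × 0.7048) / 0.7013 = 1.28, power 90.0%.
- 41% v 49.6%: (0.086 × 22.80 − 1.96 × 0.7040) / 0.7013 = 0.83, power 79.6%.

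Both agree with the plan, so the unadjusted design does what it says.

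**2. Baseline covariates only.** Adjustment reduces the variance of the marginal risk difference by about the factor (1 − R²), so n per arm is replaced by 520/(1 − R²).

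| Assumed R² | Effective n per arm | Power, 51% | Power, 49.6% |
|---|---|---|---|
| 0 (as planned) | 520 | 90.0% | 79.6% |
| 0.02 | 531 | 90.6% | 80.4% |
| 0.05 | 547 | 91.4% | 81.6% |
| 0.10 | 578 | 92.8% | 83.7% |

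The gain is about 1 to 4 points.

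**3. Adding 4-week status.** Let *a* and *b* be the probabilities of abstinence at 3 months for those abstinent and those smoking at 4 weeks. Then

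a = (0.41 − 0.47b)/0.53 and R² = 0.53 × 0.47 × (a − b)² / (0.41 × 0.59).

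| Assumed b | a | R² | Power, 51% | Power, 49.6% |
|---|---|---|---|---|
| 0 (relapse only) | 0.774 | 0.62 | 99.9% | 99.5% |
| 0.10 | 0.685 | 0.35 | 98.1% | 93.4% |
| 0.20 | 0.596 | 0.16 | 94.3% | 86.1% |
| 0.25 | 0.552 | 0.09 | 92.6% | 83.4% |

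A simulation of the standardised risk difference (4000 runs per scenario) gave 99.6%, 93.9% and 85.5% for the 8.6-point effect at b = 0, 0.10 and 0.20, in line with the formula. It did not model the unconcealed early rounds.

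**4. Where 4-week status sits in time.** The order is baseline, randomisation, 4-week data, envelope opened, 3-month outcome. The covariate precedes the booklet but follows allocation. In the first five rounds it was also collected by staff who knew the allocation; Statistical analyses puts the intervention-group participants consented before the change at 94, which is 94/520 = 18% of a planned arm.

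**The case against.** An unadjusted logistic comparison in a 1:1 randomised trial is valid, and this one reaches its stated power. A more efficient estimator may be only a matter of preference, and a SAP is still to come. The first part stands: nothing is misstated and the trial is not underpowered by this choice. The last part stands only partly, because the protocol does not leave the matter open. It fixes no baseline adjustment and gives a reason that does not bear on precision.

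Three stronger readings are tempting, and the document does not support them.

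- *A reader might infer that the plan rules out all covariate adjustment.* The sentence concerns baseline covariates in the randomised comparison and is qualified as a priori. It does not mention 4-week status, and the observational comparison is adjusted.
- *A reader might infer that adjustment would correct selection from the five unconcealed rounds.* Adjustment deals only with imbalance in what is measured. If knowledge of allocation affected who consented or how 4-week status was recorded, conditioning on that status may leave bias or add to it. CO validation of reported abstainers limits this without removing it. The protocol already plans a sensitivity analysis for these rounds.
- *A reader might infer from the plan's relapse model that the trial forgoes the equivalent of 2.6 times its sample (1/(1 − 0.62)).* That needs no 4-week smoker to be abstinent at 3 months. The plan uses the relapse rate only to obtain a control proportion. Support may run to 12 weeks, and the endpoint is 7-day point prevalence, so late quitting is possible and its rate is not given.

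**Conclusion.** The point holds as one of efficiency. The plan leaves the randomised comparison unadjusted on expected balance alone and forgoes precision that data already collected could supply. With baseline predictors the gain is modest: about 1 to 4 points of power, resting on an assumed R² of 0.02 to 0.10 and a two-sided 5% level.

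The large gains come only from 4-week status and depend on a late-quit rate that the document does not give: for 8.6 points, about 86% power if 20% quit late, 93% if 10% do and 99.5% if none do. Because that variable is post-randomisation, is a secondary outcome and was not always collected with allocation concealed, it should not enter the primary model without safeguards. Confidence is high on what the plan says and on the direction of the effect, and moderate on its size. The change is worth making, but the trial's validity does not depend on it.

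**What to change.** 1. **Primary model.** Logistic regression of 3-month validated abstinence on arm plus a short, named list of baseline predictors already in Table 1 (smoking behaviour, motivation, quit confidence). State how each is coded and how missing baseline values are handled.
2. **Estimand.** Report the standardised (marginal) risk difference and OR with 95% CIs. The coefficient from an adjusted logistic model is a conditional OR, which differs from the unadjusted OR, so it should not be the headline figure.
3. **Sensitivity analysis.** Keep the unadjusted comparison.
4. **Optional further analysis.** Add 4-week CO-validated status, justified by its being recorded before the envelope is opened. State that it is post-randomisation and a secondary outcome. Repeat this analysis without the first five rounds in both arms.
5. **Rationale.** Replace the balance argument with one based on precision.

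The cost is one sentence changed in the protocol and one paragraph in the SAP, settled before the groups are unblinded. No further data are needed. The one small drawback is the extra step of standardising to marginal estimates.

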### Randomisation

After the screening visit, but before the 4-week follow-up, all smokers who agreed to see the SCP will be randomised to either continued SBP or intervention using concealed allocation. The randomisation sequence (1:1 in permuted blocks of random size up to size 6) will be generated using a computer random-number generator and participants allocated sequentially, overseen by the University of Nottingham clinical trials unit.

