### Ethical approval, research governance, trial sponsorship and registration

This study was approved by the East Midlands-Derby Research Ethics Committee (REC reference: 18/EM/0199) and HRA/HRCW on 31 August 2018. Subsequent amendments are detailed in table 2.

**Table 2 T2:** Summary of ethical amendments

Protocol	Date	Summary of changes
V2	16 October 2018	Re-formatting of consent forms to fit within one A4 page (minor).
V2.1	29 March 2019	Amendment to letters informing/seeking guidance from participants’ general practitioner regarding potential contraindications for nicotine replacement therapy and requesting varenicline prescriptions.
		Minor amendments to interview topic guides.
		Change to incentive amounts.
		Audio recording of a sample of initial consultation interactions (substantial).
V2.2	03 June 2019	Change timing of consent to YESS trial—not implemented.
V2.1	26 July 2019	Submission of YESS subsection 1 and 2 participant information sheet (V.1 17 05 2019) as they were omitted from the original application (substantial).
V2.2	11 November 2019	Reduction in recruitment target from 2019 to 1040 to reflect the number of smokers enrolling in YLST (substantial).

YESS, Yorkshire Enhanced Stop Smoking; YLST, Yorkshire Lung Screening Trial.

This study was adopted onto the National Institute for Health Research trial portfolio on 18 September 2018 and is sponsored by the University of Nottingham. Any planned modifications to the protocol will be approved by the REC before they are adopted by the study. An audit trail of ethical amendments, documentation and data collection will be kept to allow monitoring by the research team and external regulatory bodies.

The trial was registered with the International Standard Randomised Controlled Trial Number (ISRCTN) on 25 September 2018 and the National Institutes of Health ClinicalTrials.gov database on 21 November 2018.

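### The sensitivity analysis for the unconcealed early rounds, as worded, drops early participants from the intervention group only; it should drop them from both groups

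*Protocol article*

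**What the plan says.** All references are to the protocol article.

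- **Order of events.** Under Randomisation: "After the screening visit, but before the 4-week follow-up, all smokers who agreed to see the SCP will be randomised". Under Blinding: "Consent is taken at the 4-week visit by the SCP". Consent therefore follows allocation.
- **The problem.** Blinding states: "For five rounds at the start of the trial, SCPs were aware of trial allocation at the time of consent/data collection". It names no group.
- **The remedy.** From the sixth round on, "the personalised risk information booklet (further detail provided later) or a blank booklet are enclosed in a sealed envelope", opened only after consent and data collection. This applies to both groups.
- **The promise.** On the early rounds, Blinding adds: "The impact of this will be assessed in a sensitivity analysis".
- **The rule.** Statistical analyses gives the only such analysis: "we will analyse excluding those who were consented to the intervention group prior to change in timing of consent (n=94". No other text excludes SBP participants from the same rounds.
- **The model.** The same section plans logistic regression with no baseline adjustment, relying on randomisation for balance.

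**The concern.** A practitioner who knows the allocation before consent can, without intending to, influence who enters the trial and what is recorded at that visit. This can happen in either group. A check on its effect should set aside everyone enrolled under those conditions.

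The rule as worded sets aside only the intervention side. Two things follow. SBP participants consented without concealment stay in the comparison. Group also becomes entangled with calendar period, because the intervention group then holds late participants only while the SBP group holds early and late ones. That is no longer a concurrent randomised comparison, and the model has no term to correct for it.

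This is the one analysis the article offers to show that its result is robust to a concealment lapse it openly reports. If the analysis is lopsided, agreement with the primary result may reassure falsely, and disagreement may alarm falsely.

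**Working it through.** **Inputs**

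- From Sample size: 1040 participants; quit rate 41% under SBP; 90% power for 51% and 80% for 49.6%.
- From Randomisation: allocation "1:1 in permuted blocks of random size up to size 6", hence about 520 per group.
- From Statistical analyses: 94 excluded.
- Assumed: two-sided 5% significance level; about 94 early SBP participants to match 94 early intervention participants; late rounds free of distortion; true effect zero; late quit rate 41%. The early/late differences are illustrative, as the article gives none.

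**1. The plan's own power figures**

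Power = Φ{[d − 1.96·√(2·p̄(1−p̄)/n)] / √[(p₁(1−p₁)+p₂(1−p₂))/n]}

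For 41% v 51% and n = 520: p̄ = 0.46; 1.96 × √(0.4968/520) = 0.0606; denominator √(0.4918/520) = 0.0308; (0.1000 − 0.0606)/0.0308 = 1.28; power 90.0%. For 41% v 49.6% the same formula gives 79.6%. Both agree with the article.

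**2. Share removed**

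94/520 = 18.1% of the intervention group, leaving 520 − 94 = 426 against 520.

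**3. Bias under each rule**

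Let w = 94/520 = 0.181. Let a and b be the amounts by which the early quit rate departs from the late one in the intervention and SBP groups.

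- All data: w(a − b)
- Rule as worded: −w·b
- Early participants excluded from both groups: 0

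| Early rates, intervention v SBP | All data | As worded | Both excluded |
|---|---|---|---|
| 46% v 36% (bias shared equally) | +1.8 | +0.9 | 0 |
| 51% v 41% (intervention only) | +1.8 | 0 | 0 |
| 41% v 31% (SBP only) | +1.8 | +1.8 | 0 |
| 51% v 51% (period effect only) | 0 | −1.8 | 0 |
| 31% v 31% (period effect only) | 0 | +1.8 | 0 |
| 46% v 46% (period effect only) | 0 | −0.9 | 0 |

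Figures are percentage points. First row in full: intervention (94 × 0.46 + 426 × 0.41)/520 = 41.9%; SBP (94 × 0.36 + 426 × 0.41)/520 = 40.1%; difference 1.8. Dropping only the early intervention participants gives 41.0 − 40.1 = 0.9.

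In the first three rows the share of bias left is half, none and all. In the last three the full analysis has no bias and the rule creates one.

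**4. Precision under each rule**

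| Analysis set | 41% v 51% | 41% v 49.6% |
|---|---|---|
| As worded, 426 v 520 | 86.8% | 75.4% |
| Both groups, 94 each: 426 v 426 | 83.5% | 71.3% |
| Both groups, 94 in total: 473 v 473 | 87.1% | 75.8% |

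**The case against.** The strongest reply is that 94 may be the total over both groups, loosely described. Blinding promises to assess the impact of the early rounds as such, which fits that reading. The exclusion would then be symmetric and the bias argument would fall away. This stands as a possibility. Even so, the sentence would say something other than what is meant, and an analyst who follows it would drop one group only.

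It is also fair to say that this is a sensitivity analysis, that the early/late differences above are assumed, and that a detailed analysis plan is still to come. All of that limits the weight of the point. But the article does not leave the rule open: it fixes one, with a count, and a later plan that copies it inherits the flaw. The planned descriptive comparison of baseline characteristics is some check on selective consent, but it is described for the randomised groups as a whole, not for the early rounds.

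Three stronger readings are tempting and are not supported:

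- A reader might infer that half of the bias is left in place. That holds only if both groups contribute equally, and the article does not say where any bias lies.
- A reader might infer a contradiction with Table 2, where a June 2019 entry reads "Change timing of consent to YESS trial—not implemented". That table is an amendment log, and nothing shows that Statistical analyses refers to that entry. Opening the envelope after consent can itself be loosely called a change of timing. The term is imprecise, not shown to be contradictory.
- A reader might take it as stated that both groups were affected. Blinding names no group; that both were is an inference, though a well-supported one given the blank booklet.

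**Conclusion.** The point holds as a badly worded rule. Read literally, the analysis keeps SBP participants enrolled under the same unconcealed conditions as the intervention participants it removes. It retains the control-group part of any bias, from 0% to 100% of the total in the cases where the bias favours the intervention. It can also introduce a period bias of about 0.9 or 1.8 points for an assumed 5 or 10 point early/late difference, against the 8.6 point increase that the trial is sized to detect with 80% power.

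These sizes rest on 520 per group, on 94 being the intervention count and on a similar number of early SBP participants. The article confirms neither of the last two.

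A reader might go on to doubt the primary result on this ground. The documents do not support that step: the primary intention-to-treat analysis and the sample size, which reproduces, do not depend on this rule.

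**What to change.** Reword the sentence so that the sensitivity analysis excludes all participants, in both groups, from the rounds before sealed envelopes were introduced. In the same place:

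- Define the cut by round, so that it applies identically to both groups and matches whether consent was taken without an envelope. Randomisation date alone is not clearly right: randomisation precedes the 4-week consent visit, so someone randomised before the change could have been consented with an envelope.
- State whether 94 is one group or both, and give the number in each.
- Describe the cut-point as the introduction of sealed envelopes, in line with Blinding.

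A group-by-period interaction, and a comparison of consent rates between groups within the early rounds, are optional. With an early subset of roughly 18%, the interaction would be imprecise.

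The cost is one sentence and some precision in this sensitivity analysis. If 94 is one group and early SBP numbers are similar, power for 41% v 51% is 83.5% instead of the 86.8% of the rule as worded. If 94 is the total over both groups, it is 87.1%.
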